### Randomisation

ACCHSs will be categorised into three strata based on their remoteness using ASGC-RA^35^ : (1) urban and inner regional; (2) outer regional and remote; (3) very remote. Service names will be replaced by consecutive numbers. Within each stratum, half the services will be randomised by a computer program into the early support arm and half into the late support arm. Randomisation will be conducted by an author (TD) who is blind to services’ names.

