#### Sample size

Sample size requirements were calculated using PASS (Power Analysis and Sample Software).^36^ Because larger numbers are needed to be able to determine increases in treatment provision than to demonstrate an increase in screening, the treatment provision outcome was used for sample size calculation. In an ACCHS of 1000+clients per year, approximately 60% (n=600) are likely to be aged 16 years or older.^37^ We estimate that 57% of clients (n=342) have likely been screened for alcohol use within 12 months^16^ and at least 25% (n=86) of screened clients are likely to be drinking above NHMRC recommended limits.^14 38 39^ In the late support arm, it is likely that 60% (n=51) of identified unhealthy drinkers will have an alcohol intervention recorded.^16^ Assuming an intra-cluster correlation coefficient of 0.04,^40 41^ enrolling 10 early support services and 10 late support services will allow for an increase in treatment provision over a 12-month period of at least 13% in the early support services to be detected (ie, from 60% to 73%; 80% power and 2-sided significance of 0.05). We will enrol an additional service in each arm to allow for the possibility of clusters dropping out of the study. Accordingly, the target number of services to be enrolled is 22.

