#### Quantitative data

Non-identifiable data on episodes of screening, alcohol care and related variables (see below) will be extracted from the Communicare database of each ACCHS on the 28th day of every second month throughout the 5-year trial (figure 4). The baseline extraction will include data for 12 months before the trial starts. Participating services use structured query language (SQL) queries developed for this project to extract routinely collected data. For every 2-month period a denominator sheet will be extracted which includes the date of the last visit for each client who has attended during that period and their gender and age. In addition the following variables will be extracted, each one linked to an individual client ID and the date the variable was recorded: AUDIT-C responses; the clinicians’ perception of the client’s drinking status (‘Ex-drinker’, ‘Non-drinker’, ‘Within safe drinking limits’ or ‘Unsafe - needs intervention’); whether a brief intervention, or a counselling session for alcohol use was provided; whether a relapse prevention medication was prescribed (ie, acamprosate, naltrexone or disulfiram); and if measured, a range of biological markers which may be affected by alcohol consumption (BP, HbA1C and GGT).

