#### Quantitative

Only the routinely collected data on Indigenous Australian clients aged 16+ years who have attended a participating ACCHS in the last 12 months will be included in analysis to assess:

The odds of a client being screened using AUDIT-C at least once in any 2-month period (considering those who attend in that period).The odds of a client being recorded as receiving treatment for unhealthy alcohol use at the ACCHS, including advice/education or counselling, relapse prevention medicines.The number of clients identified by ACCHS staff to have unhealthy alcohol use:via AUDIT-C: using cut-offs recommended for ACCHSs by the Australian Institute of Health and Welfare (3+ for a woman, 4+ for a man).^23^
and/or staff perception of drinking status (eg, safe, unsafe, non-drinker or ex-drinker).

We will use statistical packages, IBM SPSS for descriptive analyses and R for multi-level modelling.

Multi-level modelling will be used to account for clustering of observations under clients, who are nested within services. We will assess if clients are more likely to be screened for risky alcohol-use and provided with treatment if they are attending a service receiving support.

Two dummy variables will be constructed to indicate whether or not clients were screened with the AUDIT-C during each 2-month data extraction period, or if they received treatment. These variables will be used as outcomes in multi-level logistic regressions. As data are aggregated at bimonthly intervals, repetitive screenings within those 2-monthly periods will not influence the modelled effect of the intervention. However, to ensure that the intervention is associated with increased odds of appropriate screening, we will create a dummy variable indicating whether a client has been screened in the previous 12 months, and use this variable as the outcome in a multi-level logistic regression.

Characteristics of ACCHSs, such as number of clients, will be compared descriptively between the early/late-support services. Characteristics that display major imbalance between arms will be considered as adjustment factors in outcome analyses. As data are collected as part of routine clinical activity, missing data are likely to be non-random, as such multiple imputation will not be performed.

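### Adjustment factors are to be chosen by observed imbalance between arms, a rule with no threshold or list that would almost never pick the remoteness strata and names no baseline term

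*Protocol article*

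**What the plan says.** The Analysis section (Quantitative) says that service characteristics, with client numbers as the one example, will be compared descriptively between the arms. It continues: "Characteristics that display major imbalance between arms will be considered as adjustment factors in outcome analyses". It does not list the candidate characteristics or define major imbalance, and it does not say whether the adjusted or the unadjusted result is primary.

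Two other sections bear on the rule:

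- **Randomisation.** Services are placed in three remoteness strata. "Within each stratum, half the services will be randomised by a computer program into the early support arm", and the other half go to late support.
- **Data collection, Quantitative data.** Extraction runs every second month. "The baseline extraction will include data for 12 months before the trial starts".

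The Analysis section describes multi-level logistic regressions on whether a client was screened, or treated, in each 2-month period, with observations nested in clients and clients in services. It mentions neither remoteness nor a baseline rate as a model term. It does not say whether the pre-trial 2-month periods enter the model as outcomes.

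**The concern.** The rule has three weaknesses.

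1. **It selects on the wrong property.** With about 11 services per arm, sizeable chance differences are to be expected. A difference between arms says nothing about whether the characteristic predicts screening or treatment. Covariates gain precision by being prognostic, whether or not they are imbalanced.
2. **It leaves the model open.** The threshold, the candidate list and the decision to adjust are all left to judgement after the arms have been compared, in a trial where participants and staff cannot be blinded.
3. **It works against the design.** Remoteness is balanced by construction, so a rule triggered by imbalance would almost never pick it, however prognostic it is.

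What is at stake is precision and the credibility of the adjusted estimate. The number of services largely sets this trial's precision, so a service-level covariate that explains outcome variation could be worth several points of power.

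**Working it through.** **Inputs, all from Sample size.** The effect, power and alpha are "from 60% to 73%; 80% power and 2-sided significance of 0.05". Cluster size is m = 86 ("at least 25% (n=86) of screened clients are likely to be drinking above NHMRC recommended limits"). The ICC is 0.04 ("Assuming an intra-cluster correlation coefficient of 0.04"). The calculation rests on "enrolling 10 early support services and 10 late support services"; 22 services (11 per arm) are to be enrolled. These inputs concern treatment provision, a secondary outcome. The article gives no such inputs for AUDIT-C screening.

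**Step 1: reproduce the plan's figure.**
- Design effect = 1 + (86 − 1) × 0.04 = 4.4.
- Effective n per arm = 10 × 86 / 4.4 = 195.5.
- SE = √[(0.60 × 0.40 + 0.73 × 0.27) / 195.5] = √(0.4371 / 195.5) = 0.0473.
- Normal-approximation power = Φ(0.13 / 0.0473 − 1.96) = 0.785, and the detectable difference is 13.2 points. This agrees with the stated 80% and 13 points to within 2 points of power.
- With a t reference on 18 df, power is 0.739. With 11 per arm, SE = 0.0451 and t-based power on 20 df is 0.783.

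**Step 2: how much of the variance is between services.** Share = ICC × m / design effect = 0.04 × 86 / 4.4 = 0.78.

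**Step 3: baseline adjustment (illustrative).** Let r be the service-level correlation between baseline-year and follow-up rates. The article does not give r, so a range is assumed. The variance is multiplied by (1 − r²). Three df are spent: two for strata and one for the baseline rate. Any variance explained by the strata is ignored here.

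| Model | Power, 10 per arm | Power, 11 per arm |
|---|---|---|
| Unadjusted | 0.739 (18 df) | 0.783 (20 df) |
| Adjusted, r = 0 | 0.729 (15 df) | 0.776 (17 df) |
| Adjusted, r = 0.3 | 0.768 | 0.813 |
| Adjusted, r = 0.5 | 0.843 | 0.880 |
| Adjusted, r = 0.7 | 0.949 | 0.967 |

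**Step 4: omitting the strata (simulation).** 22 services, assumed strata of 8, 8 and 6, 1:1 within stratum, analysed as service means. The share of service-mean variance due to strata is assumed.

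| Share due to strata | Type I error, strata ignored | Power, strata ignored | Power, strata in model |
|---|---|---|---|
| 0% | 0.051 | 0.78 | 0.78 |
| 10% | 0.042 | 0.79 | 0.82 |
| 20% | 0.028 | 0.80 | 0.86 |
| 30% | 0.019 | 0.81 | 0.90 |

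With strata in the model, type I error stays at about 0.05. Ignoring strata that explain 10% to 30% of the variance costs about 3 to 9 points of power.

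**Step 5: imbalance-triggered selection (simulation).** 22 services, simple randomisation, five assumed prognostic covariates, adjustment when a standardised difference exceeds 0.3 or 0.5 SD.
- A fixed prespecified set has type I error of about 0.05.
- Always using the selected model gives about 0.03.
- Reporting the better of the adjusted and unadjusted results gives 0.065 to 0.069.

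**The case against.** The strongest reply is that this is a condensed article. It lists no fixed effects at all, and strata and baseline terms are commonly set out in a full protocol or SAP. That stands: a reader might infer that remoteness and baseline are excluded from the outcome model, but the article does not say so. The point therefore rests on the imbalance rule, which the article does state.

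Second, the baseline data may already be used. If the pre-trial 2-month periods are outcomes in the repeated-measures model, the service random effects carry the baseline information, and a baseline-rate covariate would use the same data twice. This stands too, and the fix has to allow for it.

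Third, a reader might take baseline rates to be the strongest predictors available. The article does not support that for AUDIT-C. The Introduction says AUDIT-C became a national key performance indicator only in July 2017, and the section on practice software support says it was not routine in the standard health check when the trial began. Baseline AUDIT-C rates could be low and weakly predictive.

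Fourth, a reader might infer a raised false-positive rate. Omitting strata does the opposite. Inflation appeared only where the better of two results was reported. The article does not plan that, although its wording does not prevent it.

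None of these replies defends a rule with no threshold or list that selects on imbalance.

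**Conclusion.** The point holds as a weakness in a rule that the article states. Selecting covariates by unspecified major imbalance is a poor basis for adjustment with about 11 services per arm. It leaves the adjusted model to post-hoc choice and would almost never select the stratification factor.

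The cost is lost precision. Omitting strata that explain 10% to 30% of the variance of a service mean would cost about 3 to 9 points of power and make the test conservative. For treatment provision with 11 services per arm, baseline adjustment would raise power from 0.78 to between 0.81 and 0.97 for r = 0.3 to 0.7, and would lower it by about one point if r = 0. The correlation, the share due to strata and the strata sizes are assumptions. The 78% between-service share follows from the plan's own m and ICC. The gain for the primary outcome cannot be sized from the article.

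The stated sample size is not wrong on this account; it reproduces without any adjustment.

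**What to change.** Replace the quoted sentence with:

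> The primary outcome models will include remoteness stratum (three levels) as a fixed effect and will account for each service's baseline level of that outcome, either as a service-level baseline-rate covariate or, where the pre-trial 2-month periods are included as outcomes, through the modelled baseline periods (not both). Covariates prompted by observed imbalance will be used only in a sensitivity analysis.

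The data are already to be extracted, and the strata are fixed at randomisation. The cost is about 3 service-level degrees of freedom (two for strata, one for a baseline-rate covariate), or about one point of power if none of these terms proves prognostic. The article's Protocol amendments section already provides a route for registering the change.

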**Figure 2 F2:**
[figure not shown]
Flow diagram for the trial.

The support provided will contain eight core elements (table 1), but be tailored, guided by ACCHSs, to their individual needs, including needs by remoteness. It will also be underpinned by current evidence such as national alcohol treatment guidelines,^10^ Alcohol Treatment Guidelines for Indigenous Australians^31^ and national alcohol consumption guidelines.^14^ The study methods will be based on principles of conducting health research with Indigenous Australians.^32^ This includes Indigenous involvement and engagement, benefits for Indigenous peoples, and led by Indigenous Australians.

**Table 1 T1:** Eight core support elements*

1	Service champions	Services asked to nominate two representatives to act as advocates of alcohol care and links between the service and research team
2	National workshop	National capacity building workshop for service champions at the start of the support phase (and for early support services, a wrap-up feedback workshop at the end of the maintenance support phase)
3	Onsite training	Training will be offered to each ACCHS at their service
4	Resources/funding	Some resources (eg, visual resources for brief intervention and clinical guidelines) will be given to services for free. Additional funding will be provided for the selection and purchase of further resources (eg, FASD doll, standard drink cups).
5	Practice software support	Support will be provided to services throughout the trial to facilitate the routine clinical use of alcohol-related items in the practice software.
6	Data feedback	Individual service data will be fed back to each service every second month
7	Phone conferences	Phone conferences will be held every second month between service champions and project team (including an addiction medicine physician). These will allow sharing of ideas and joint problem solving.
8	Online platform	Further resources and information will be shared via a secure online platform.

*These eight core elements of support will be tailored to local service needs. Further detail on each element is provided in the body of the text.

ACCHS, Aboriginal community controlled health service.

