### The model of support

ACCHSs will be acknowledged as the experts in cultural healthcare for Indigenous peoples in their communities and Australia. The study also recognises the need for flexibility based on needs of individual services and of the ACCHS sector as a specialist sector overall. Support approaches will include the same core elements (table 1). However, approaches will be tailored to the needs of each ACCHS, for what works best for their service, clients and communities.

The core support elements were designed based on evidence-based approaches for supporting implementation of alcohol care.^21 29^ The project team also drew on their experience working within (six authors) and with Aboriginal health services; and in health workforce development (nine authors). Advice was also received from ACCHS peak organisations and networks in New South Wales and South Australia, and from a research team conducting a quality improvement trial for ACCHSs on diabetes screening.^42^

At the start of the early support phase, the support will be refined based on preliminary analysis of qualitative data from staff interviews and after feedback from the initial national workshop for early support service representatives. Tailoring and further minor refinement of support will occur during the trial, informed by service feedback.

Early support (‘intervention’) services will receive the support soon after the trial starts (1 year of active support, 1 year maintenance phase). Late support (wait-control) services will receive the same intervention elements 2 years after the start of the early-support phase. Due to the nature of the intervention, it is not possible to blind participants or staff as to which services are receiving support.

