All analyses will be repeated for the maintenance phase of the study to see if study effects weaken or strengthen over time. The analysis will also be repeated after the late support services have received support, to see if any effect on use of screening or treatment can be replicated.

If a significant effect of the support on alcohol care outcomes is demonstrated, a secondary analysis will examine the elements of support which were most effective, and whether the effect of support changed over time during a support phase. Potential change in client health indicators over time (AUDIT-C scores, GGT, HbA1C, BP) will be examined in relation to support provision.

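### Repeating the analyses in the maintenance year gives two correlated effects but no estimate or interval for how the effect changed

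*Protocol article*

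**What the plan says.** Early support services receive "1 year of active support, 1 year maintenance phase" (The model of support). Late support services start two years after the early ones, so both years are randomised comparisons. The screening and treatment indicators are built for each 2-month extraction, and "These variables will be used as outcomes in multi-level logistic regressions" (Analysis, Quantitative).

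On persistence, the same section says: "All analyses will be repeated for the maintenance phase of the study to see if study effects weaken or strengthen over time". This names a question and the method meant to answer it. No joint model, arm-by-phase term or interval for the difference between phases is attached.

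The next paragraph adds a second piece: "If a significant effect of the support on alcohol care outcomes is demonstrated, a secondary analysis will examine" which elements of support worked best and "whether the effect of support changed over time during a support phase". No model or contrast is given for it.

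The sample size section bases power on treatment provision over one 12-month period and says that screening needs smaller numbers.

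**The concern.** Whether an effect weakens or strengthens is a question about the difference between two effects. Two separate fits each answer whether there is an effect in that year. The same services, and presumably many of the same clients, contribute to both years, so the two estimates are correlated. Separate fits do not estimate that correlation, so a valid interval for the change cannot be built from their outputs.

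At stake is what can be said about persistence. The Discussion suggests that the model could be sustainable and scaled up for longer-term support. The maintenance year supplies the randomised evidence on whether the effect lasts after active support, because the control arm receives support afterwards. With separate fits, a constant effect can look as if it faded or grew, and a real loss can go unnoticed.

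**Working it through.** **1. The plan's own power figure.** Inputs from Sample size: "enrolling 10 early support services and 10 late support services", 86 unhealthy drinkers per service, ICC 0.04, and "from 60% to 73%; 80% power and 2-sided significance of 0.05".

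- Design effect = 1 + (86 − 1) × 0.04 = 4.40.
- Effective n per arm = 10 × 86 / 4.40 = 195.5.
- SE = √[(0.60 × 0.40 + 0.73 × 0.27) / 195.5] = 0.0473, and 0.13 / 0.0473 = 2.75.
- Power = Φ(2.75 − 1.96) ≈ 78.5%. With pooled variance, the rise detectable at 80% power is 13.3 points.

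The stated 80% for a 13-point rise is reproduced to rounding, so 80% per year is a fair working figure for treatment provision in one phase.

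**2. Equal true effects, compared by significance.** Assumptions not in the protocol: the comparison is made by significance, and the two z statistics are bivariate normal with correlation ρ. Each has mean 1.96 + 0.84 = 2.80, which is 80% power. Then

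P(significant in active year, not in maintenance) = 0.80 − P(both significant).

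| ρ | P(both significant) | False waning | False growth |
|---|---|---|---|
| 0 | 0.640 | 16% | 16% |
| 0.5 | 0.687 | 11% | 11% |
| 0.8 | 0.729 | 7% | 7% |

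ρ = 0 is a limiting case, since the same services supply both years. For screening, power per year should be higher. At an illustrative 95%, false waning is 4.8%, 3.8% and 2.5% for the same three correlations.

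**3. Simulation of the sample-size design.** 10 services per arm, 86 clients per service, ICC 0.04, 60% v 73% in both years, service-level t tests, 20,000 runs, and between-year correlation of the service effects varied from 0 to 1. Power per year was about 74%.

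- False waning by significance: 9% to 20%.
- The arm difference moved by 5 points or more between years, by chance alone: 11% to 45%.
- A direct test of the change in the arm difference rejected in 4.9% to 5.3%, as it should at the 5% level.

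**4. The opposite error.** If half the effect is truly lost, the bivariate normal calculation gives both years significant in 23% (ρ = 0) to 29% (ρ = 0.8 or 0.9) of trials.

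**5. What a direct contrast can detect.** In units of one year's SE, the change has SD √[2(1 − ρ)]. For loss of half the effect, the standardised change is 0.5 × 2.80 / √[2(1 − ρ)].

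- ρ = 0: 1.40 / 1.41 = 0.99, power 17%.
- ρ = 0.5: 1.40 / 1.00 = 1.40, power 29%.
- ρ = 0.8: 1.40 / 0.63 = 2.22, power 60%.

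**The case against.** **Change over time is already planned.** A reader might infer that the protocol has no analysis of change. It has one, as quoted above, and it may cover both years: Table 1 places "a wrap-up feedback workshop at the end of the maintenance support phase", while the Workshops text places the same event at the close of the early services' support phase. Read together, these suggest that the support phase includes maintenance. This stands as mitigation, not as a cure. Elsewhere the article also speaks of an active support phase, so the span is not settled. The analysis names no contrast, and it runs only after a significant effect. That condition is reasonable for waning, but it would miss an effect that emerges late. The weaken-or-strengthen question stays tied to repetition.

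**No decision rule is stated.** A reader might infer that the plan will declare waning when the first year is significant and the second is not. The text does not say so; comparing two odds ratios with their intervals fits it equally well. The percentages in step 2 therefore show what would follow under one assumed reading. Comparing point estimates is not clearly safer (step 3), and overlap of separate intervals ignores the correlation.

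**The size is easily overstated.** Adding both directions gives 32%, 23% and 14% (2 × 16.0, 2 × 11.3 and 2 × 7.1), but the rate of false waning is half of each. The 80% power belongs to treatment provision, not to the primary outcome.

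**Detail belongs in an analysis plan.** Leaving out a model term would be no finding in a condensed article. Here, however, the article fixes a method for a named question, and that method does not answer it.

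**Conclusion.** The point holds as a moderate one on a secondary question. Repetition by phase does not estimate the change it is meant to show, and the later secondary analysis does not clearly repair this. Its size depends on assumptions the protocol does not supply: comparison by significance, 80% power in each year, and between-year correlations of 0 to 0.8. Under these, false waning occurs in about 16% down to 7% of trials, with the same chance of false growth and lower rates for screening.

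The documents do not support the stronger inferences that persistence is a declared aim or that the main result is at risk. Neither the Aims nor the registered outcomes include sustainability, the Discussion claims only potential, and the primary comparison is untouched.

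**What to change.** Replace the repetition sentence with one joint analysis. Fit a multi-level logistic model to all 2-month periods of the two randomised years, with arm, 2-month period, an arm-by-phase term (active v maintenance), and the planned client and service random effects. Add a service-level random effect for phase, so that services may differ in how they change and the interval is not too narrow. Report the arm-by-phase ratio of odds ratios with its 95% CI, whether or not the first-year effect is significant. Take the phase-specific effects from the same model, and make no claim of waning or growth from separate p-values. State whether the later analysis of change within a support phase is this contrast or a different one.

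The cost is a few sentences and a somewhat more complex model with about 22 clusters. The 2-monthly data and multi-level modelling in R are already planned, so no new data or services are needed. The interval may be wide: under assumed correlations of 0 to 0.8, power to detect loss of half the effect is about 17% to 60%. The plan should say so in advance, so that an inconclusive interval is not read as persistence.
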